### Outcomes

The primary outcome will be the mean difference (MD) in home SBP at 12 months, from baseline values. Secondary outcomes will include (1) proportion of patients with SBP within guideline target at end of the study, from baseline; (2) Proportion of patients who remained within target SBP throughout the study; (3) user acceptability of HBPT for BP control; (4) cost-effectiveness and cost utility of HBPT combined with a protocol-based case management approach, and (5) adverse events reported.

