## Methods

### Study Objectives

The primary aim of this study is to assess the mean difference in SBP at 12 months, from baseline in remote communities in Northern Alberta through a pragmatic RCT, comparing HBPT + usual care versus HBPT + a case manager. Secondary aims of the study will include:

Proportion of patients who maintained home SBP within guideline target (<130 mmHg)^10,11^ from baseline to the end of the study.Proportion of patients who remained within guideline target SBP (<130 mmHg),^10,11^ throughout the study.The user acceptability of HBPT for BP control, using a qualitative approach.The cost-effectiveness and cost utility of HBPT combined with a protocol-based case management approach among remote-dwellers with CKD compared to the usual care.5.Proportion of adverse events, eg, syncope, hypotension requiring assistance or medical attention, worsening of kidney function (2x serum creatinine or 50% decline in estimated glomerular filtration rate [eGFR]), and/or electrolyte abnormalities [hyperkalemia ≥ 6.5 mmol/L], in each arm of the study.

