#### Intervention arm

Due to the ongoing COVID-19 restrictions for face-to-face patient contact, we will train patients through phone and video contact in addition to sending each participant a written information outlining the study procedures, how to measure their BP, how to download and use the Sphygmo App, and how to transmit BP measurements from their smartphones (Supplementary Appendix 1 and 2). Thus, we will train patients to measure BP using guideline recommendations^
10
^ leveraging a locally developed and validated HBPT system (http://mmhg.ca/about-us/). Patients will receive a Bluetooth-enabled and validated electronic upper arm oscillometric BP device (A&D Ltd. UA-651BLE; San Jose, California) that will be paired to their smartphone. Instructions on how to measure appropriate cuff size will also be provided to each patient (Supplementary Appendix 2). Patients will be required to sit with their back rested for at least 5 minutes with the BP cuff around their arm. They will then be required to push the start button on the HBPT device to initiate BP measurement. HBPT values will be based on a series comprised of the mean of duplicate measures, for morning and evening, for a 7-day period and the first day home BP values will not be considered.^
11
^ Thus, mean SBP for the week will be computed from average of duplicate readings for the next 6 days, that is, 24 measurements. The BP data will be auto transmitted via Bluetooth to their smartphone and relayed to a secure web portal for review (Figure 3). This 7-day protocol will be repeated each month until BP is in the required target range. Once BP is controlled, that is, guideline-concordant, the 7-day protocol will be repeated every 3 months for 1 year. The smartphone platform is already established in 4 markets (Canada, United States, Hong Kong, Singapore) and is widely used by members of the target population^
29
^ and a similar system has been tested in a pilot study of 20 patients from the University of Alberta’s Hypertension Clinic as well as in a trial of BP telemonitoring in very elderly patients residing in supportive living environments.^
30
^

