#### Control arm

Patients in the control arm (usual care) will receive the same HBPT device and BP measurement training as those in the intervention arm and will also follow the same measurement protocol—That is, 2 measurements taken in the morning and 2 taken again in the evening for 7 consecutive days. The values from the first day will be discarded and the mean SBP for the week will be computed from the average of the readings from the following 6 days, that is, 24 measurements. However, the study case manager will not interact with patients in this group. Patients in his group will be expected to inform their PCP or nurse practitioner (NP) of their BP readings at their scheduled consultations. For those in this group whose 6-day average SBP readings are ≥ 220/110 mmHg or <70 mmHg, the case manager will notify the Data Safety and Monitoring Committee (DSMC) for urgent review, treatment plan and referral strategy. Each participant’s PCP / NP will be informed of the patient’s involvement in the trial and will receive a letter with a copy of the study synopsis and 1-page guideline summary for BP thresholds, targets, and treatments relevant for CKD.

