### Sample Size Estimation

The sample size calculation for this trial is based on the data from HBPT plus pharmacist management trial on the hypertension population.^
22
^ Adequate power will be used to detect a clinically important absolute difference in mean SBP of 10 mmHg between the intervention arm and the control arm (usual care). Using a 2-sample t-test, alpha of 0.05 and power of 0.80, and assuming a common standard deviation of 19 mmHg, the required sample size will be ~58 patients per arm, or 116 in total. Accounting for ~20% attrition over 1 year, we will recruit 73 patients per arm, for a total of 146 patients. This sample size is also powered to detect a difference of 20% in the proportion of patients who maintain the guideline target of SBP (alpha 0.05, power 80%, and assuming event occurs 50% in the control group).^
22
^

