### Plan for Data and Statistical Analysis

Baseline statistics and the outcome variables will be described using counts and proportions, mean (SD) or median (interquartile range) as appropriate. All analyses will follow the intention-to-treat principle. We will estimate the effect size as the mean difference of SBP between groups at 12 months using a mixed linear-regression model include fixed-effects term for time point (6 months and 12 months), intervention, their interaction, and a random-effect term for participants. For the dichotomous outcomes (patients who maintained the SBP guideline and adverse outcomes), we will use Poisson regression with robust error variance to test the effect of the intervention.^
50
^ Continuous outcomes without repeated measurement will be examined using linear regression. We will adjust for eGFR for all the analyses. All estimated effect sizes will be reported along with 95% confidence intervals, and P<0.05 was considered statistically significant. We will analyze the data using Stata/MP 17.0 software (www.stata.com).

We will use multiple imputation method for missing data. Imputation of missing SBP values will only apply in instances when participants do not have any blood pressure recordings for the entire week. We will impute the missing SBP within each randomized group using age and sex separately at 6 months and 12 months. Estimate from each imputed data set will be combined using Rubin’s method.^
51
^ No interim analyses are planned due to the short duration of the study. However, for subgroup analysis, we will use the model from the analysis for primary analysis to explore the relationship between intervention and eGFR groups, age groups, the presence of diabetes, and so on.

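### The plan imputes SBP only at months 6 and 12, visit by visit from age and sex, which does not fit the secondary outcome of staying at target throughout the study

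*Protocol article*

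**What the plan says.** Outcomes lists as the second secondary outcome the "Proportion of patients who remained within target SBP throughout the study". Study Objectives gives the threshold as below 130 mmHg. Neither section says which home series count.

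The measurement schedule is under Intervention arm. Before control, "This 7-day protocol will be repeated each month until BP is in the required target range". After control, "the 7-day protocol will be repeated every 3 months for 1 year". Under Control arm, control patients "will also follow the same measurement protocol". Follow-up therefore contains series at times other than months 6 and 12.

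Plan for Data and Statistical Analysis applies intention to treat to all analyses and Poisson regression with robust variance to the dichotomous outcomes. On missing data it says "Imputation of missing SBP values will only apply in instances when participants do not have any blood pressure recordings for the entire week", and then "We will impute the missing SBP within each randomized group using age and sex separately at 6 months and 12 months". Sample Size Estimation expects losses: "Accounting for ~20% attrition over 1 year, we will recruit 73 patients per arm".

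**The concern.** The outcome is a conjunction: one series at or above 130 mmHg makes the patient a failure, and success requires every relevant series to be at target. The stated imputation rule does not suit it under either plausible reading of the word throughout.

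- **All series count.** Values missing at other times, such as a skipped quarterly week between the two imputed visits, are neither observed nor imputed. A patient with no observed failure and such a gap cannot be classified, yet intention to treat keeps that patient in the analysis.
- **Only months 6 and 12 count.** The gaps are filled, but each visit is filled on its own. Whether a patient is at target at both visits depends on how strongly the two readings go together, and the named predictors leave that out.

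At stake are the reported proportions in each arm, and a scoring choice left open in a trial where participants and clinicians know the allocation.

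**Working it through.** **Plan's own figure.** Difference 10 mmHg, SD 19, two-sided alpha 0.05 (sidedness assumed), power 0.80: n = 2 × (1.960 + 0.842)² × 19² / 10² = 56.7 per arm by the normal formula. The exact two-sample t-test gives 57.6, so 58. Then 58 / 0.80 = 72.5, so 73 per arm and 146 in total. The attrition allowance is 73 − 58 = 15 per arm. The stated sample size reproduces.

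**Inputs for the illustration.** From the article: SD 19, target below 130, arm difference 10, dropout 20%. Assumed: means of 130 (control) and 120 (intervention), four quarterly series, within-patient correlation ρ = 0.6 (range 0.5–0.7), and dropout equally likely after series 1, 2 or 3 and unrelated to SBP.

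**Formula.** With a random intercept and independent visit error, the probability of being at target in k given series is p_k = ∫ φ(x) Φ((z − √ρ·x)/√(1−ρ))^k dx, where z = (130 − mean)/19. So z = 0 for control and 10/19 = 0.526 for intervention. At ρ = 0.6:

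| | p1 | p2 | p3 | p4 |
|---|---|---|---|---|
| Control | 0.5000 | 0.3524 | 0.2786 | 0.2335 |
| Intervention | 0.7007 | 0.5736 | 0.4981 | 0.4465 |

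**Reading 1: all series count.** Leavers at target in every observed series are 0.20 × (p1 + p2 + p3)/3:
- control 0.20 × 1.1310/3 = 7.5%, or 5.5 of 73
- intervention 0.20 × 1.7724/3 = 11.8%, or 8.6 of 73

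A patient who leaves after series 3 lacks only month 12, which is imputed. Dropping that group gives 0.20 × (p1 + p2)/3:
- control 5.7%, or 4.1 of 73
- intervention 8.5%, or 6.2 of 73

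Hence roughly 6–8% and 8–12%. Over ρ = 0.5 to 0.7 the two counts span 5.6–7.9% and 8.4–12.1%. Patients who stay but miss a week outside months 6 and 12 come on top.

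**Effect of the scoring rule (ρ = 0.6).**

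| Rule | Control | Intervention | Difference |
|---|---|---|---|
| All four series, complete data: p4 | 23% | 45% | 21 points |
| Months 6 and 12 only, complete data: p2 | 35% | 57% | 22 points |
| Available series: 0.8·p4 + 0.2·(p1+p2+p3)/3 | 26% | 48% | 21 points |
| Dropouts as failures: 0.8·p4 | 19% | 36% | 17 points |

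**Reading 2: only months 6 and 12 count.** Every leaver in this model lacks month 12, and some lack month 6 too. Suppose age and sex carry little of the within-patient correlation. Imputing each visit separately then gives joint success of p1 × p1 among leavers, where the model value is p2:
- control 0.5000² = 25%, against 35%
- intervention 0.7007² = 49%, against 57%

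For a control at target at month 6, the chance of being at target at month 12 is p2/p1 = 0.705, but the imputation uses 0.50. For intervention the figures are 0.819 and 0.70.

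Overall proportions become:
- control 0.8 × 0.3524 + 0.2 × 0.2500 = 33.2%, which is 2.0 points below 35.2%
- intervention 0.8 × 0.5736 + 0.2 × 0.4910 = 55.7%, which is 1.7 points below 57.4%

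Both arms fall together, so the difference changes by less than half a point.

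**The case against.** **Not every leaver is affected.** A reader might infer that the whole 20%, about 15 of 73 per arm, cannot be scored. The documents do not support that. One observed series at or above 130 mmHg settles failure whatever is missing later. Imputed month-6 and month-12 values can settle more. If they are allowed to, the undetermined leavers in an average imputed data set fall to 0.20/3 × (p1³ + p2·p1). That is 0.0667 × (0.125 + 0.176) = 2% of controls and 0.0667 × (0.344 + 0.402) = 5% of intervention patients. This stands and limits the size of the point.

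**The treatment effect is fairly stable.** Three of the four rules give an arm difference of 21–22 points; only dropouts as failures gives 17. A reader might also infer that the arm with more dropout will look clearly better under available-series scoring. In the same model, raising one arm's dropout from 10% to 30% lifts its success by just under 3 points (24.8% to 27.7% in control, 46.1% to 49.0% in intervention), and nothing in the article predicts unequal dropout. This stands too.

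**A consistent reading exists.** The article never says that every home series counts. If the outcome uses only the modelled time points, imputation reaches every missing follow-up value. That removes the undefined cases, but visit-by-visit imputation remains unsuited to a joint outcome.

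**Detail may sit in a statistical analysis plan.** The article is condensed, and scoring rules for a secondary outcome are often placed there. Silence alone would be no finding. Here, however, the article itself fixes the imputation time points and names the predictors, and those do not match the outcome it defines.

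**Quarterly timing is not clearly anchored.** Because the three-month interval starts once BP is controlled, a patient controlled at month 2 might, on one reading, have series at months 5, 8 and 11. This stands: a fixed quarterly grid cannot simply be assumed, and the fix must allow for it.

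**Conclusion.** The point holds in a limited form: the stated imputation rule does not match the stated outcome. If all series count, the observed data leave roughly 6–8% of controls and 8–12% of intervention patients unsettled through early departure, plus anyone at target in every observed series who misses another week. If only months 6 and 12 count, the outcome is defined, but leavers' joint success is understated (25% against 35%, and 49% against 57%) and each arm's proportion drops by about 2 points.

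These sizes rest on assumed means of 130 and 120 mmHg, correlation 0.6, dropout unrelated to SBP, and age and sex being weak predictors. For ρ between 0.5 and 0.7 the overall shortfall under the second reading is 1.7–2.5 points in control and 1.3–2.0 in intervention. The 20% is a planning allowance, not a forecast for this outcome. The choice of series matters most for the reported level, at about 12 points per arm between four series and two. The calculation does not show a large distortion of the arm difference. The point is worth correcting for one secondary outcome and does not concern the definition of the primary outcome.

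**What to change.** 1. State which home series define the outcome, and reconcile that with the monthly-then-quarterly measurement schedule so that no series is treated as missing when none was scheduled.
2. Impute SBP jointly across those series within each arm, with baseline SBP and the other visits' SBP in the model as well as age and sex.
3. Derive the at-target-throughout indicator in each imputed data set, fit the planned Poisson model in each, and combine by Rubin's rules.
4. Report dropouts as failures as a sensitivity analysis.
5. Fix these rules before outcome data are examined, because allocation is open.

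The cost is a few sentences of analysis wording and a somewhat larger imputation model in 146 patients. No new data collection is needed, since home readings are already transmitted. If the schedule leaves series at irregular times, the imputation model will need some care over visit timing.

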### Adverse Events and Safety Monitoring

An independent DSMC will monitor the trial for safety and efficacy. Safety concerns that will apply to this study will include any syncopal event, hypotension (SBP <110 mmHg requiring medical assistance), occurrence of severe hypertension (SBP ≥ 220 mmHg and/or DBP ≥ 110 mmHg), hyperkalaemia (serum potassium ≥ 6.5 mmol/L), and worsening kidney function (doubling of serum creatinine or 50% reduction in eGFR from baseline value). Safety concerns will be reviewed immediately by the case managers and appropriate referral, or management instituted. The DSMC will review the data regularly or as soon as cases are referred to them by the investigators and will determine if patients should continue their participation in the study.

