### Study Setting

This study will be conducted in select remote communities in the Peace River Region of Northern Alberta, located ~1,000 km from Edmonton with a population base of ~75,000 (Figure 1). The CKD population in this region receives care from a primary care network consisting of 35 primary care providers (PCPs) affiliated with 9 primary care group practices. Patients with CKD and hypertension will be identified from the Northern Alberta Renal Program (NARP) database and contacted by the study team to participate in this study.

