### Participant Recruitment

#### Study population

The following eligibility criteria will apply to this study:

Age ≥ 18 years with documented diagnosis of established CKD (not on dialysis with eGFR < 60 mL/min/1.73 m^2^ and/or proteinuria > 1 g/day)Remote dwelling patients in the Peace River region of Alberta, CanadaPatients known with hypertension (physician diagnosed / self reported and currently taking antihypertensive medications)Owning a smartphone (iOS or Android) with access to wireless internet connection.Proficiency in English language (both verbal and written); and ability and willingness to provide informed consent for participation.Ability and willingness to use the HBPT device (≥80% recordings sent in the training period)

The following exclusion criteria will apply to this study:

Patients with hypertensive urgency or emergency identified during the training period (immediate consultation will be initiated with the patient’s PCP or with a hypertension specialist)Patients with stage 5 CKD (eGFR ≤ 15 ml/min/1.73 m)^2^ or patients receiving kidney replacement therapyHeart failure with reduced ejection fractionPresence of any terminal illness (life expectancy < 1 year)Participation in any ongoing clinical drug trialPregnancy, lactation/breastfeedingPlanning to relocate out of the Peace River region or residence in an area without mobile phone coverage.

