### Study Procedures and Data Collection

At baseline, relevant demographic and health behavior information including age, sex, race, smoking, alcohol intake and details of patient’s medical history such as significant CV disease (eg, coronary artery disease, stroke, peripheral arterial disease, heart failure) and medication history (BP-lowering drugs—name, type, dosage, frequency, and duration) will be collected. Relevant clinical details such as body mass index (BMI) will also be recorded. Blood pressures will be measured and recorded following guideline recommendations.^10,11^ Other information that will be collected includes health care use in the past year (physician and/or emergency room visits, and hospitalizations) ascertained through patient self-reports and/or provincial administrative data sources, quality of life (Kidney Disease Quality of Life-36 [KDQOL-36]) and utility measurements (European Quality of life Five Dimension [EQ-5D]); and satisfaction with receiving health care, using the Patient Assessment of Care for Chronic Conditions (PACIC-2.0).^29-32^

Laboratory measurements will be carried out at baseline including serum electrolytes, serum creatinine (and estimated glomerular filtration rate), glycated hemoglobin (HbA1c), and urinary albumin/creatinine ratio (UACR). These measurements will also be taken at 6-months and 1 year.

Assessment of usability and acceptability is critical for all technology-enhanced care interventions to minimize risk of undesired consequences commonly seen post-implementation.^33,34^ End-user input into system design and operation is important throughout the evaluation process to reduce the risk that interventions will be ineffective, unusable, or unsafe. Usability testing will involve assessment of human-computer interaction—specifically, issues related to use, interface, design, function and will also include acceptability of the model of care for the caregivers. We will take a qualitative approach to this process by using focus groups. We plan to recruit 2 focus groups, 1 for patients in the telemonitoring arm and 1 for care providers (case managers and PCPs), with a target sample size of 5 to 8 participants in each group. The first 5 users typically identify 70% of severe usability problems and the first 8 users typically identify 85%; a higher sample size has low incremental yield due to data saturation.^
35

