^ and other chronic diseases.^41-43^ Best practices for economic evaluation will be followed.^41,44-46^ The intervention includes intermittent or one-time costs (eg, devices, treatment algorithm development, patient and health care professional training) and ongoing costs (eg, network and data, case manager time, BP medications). Data captured during the RCT will accurately determine the costs of telemonitoring, case management, and health care use by patients (physician, ER visits, etc.). The change in BP at 1 year, a validated surrogate, will be a key variable in both analyses:

Model A will calculate the cost per decrement in mean BP using a 1-year time horizon and a public health care payer perspective.Model B will estimate incremental cost per quality-adjusted life year (QALY) gained over a lifetime.^42,47^ It will consider longer-term health outcomes, including the probability of developing end-stage kidney disease (ESKD) (requiring dialysis or transplant) or major CV events (ie, coronary artery disease, heart failure, stroke), all-cause mortality, impacts on quality of life (EQ-5D), and health care costs associated with these outcomes.

In each model, we will explore distributions using bootstrapping, create acceptability curves, and perform one-way and probabilistic sensitivity analyses to explore the impacts of uncertainty in key model parameters. In Model B, the potential impact of reducing complications of treating hypertension in patients with CKD (hypotension, syncope) by a plausible range will be explored in a sensitivity analysis using baseline risk determined from a population-based cohort of patients^
48
^ and ambulatory care sensitive conditions^
49
^ for emergency room visits and hospitalizations.

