### Potential Challenges and Mitigation Strategies

We have identified potential challenges to this study and have prepared mitigation strategies to address them. First, although the 1-year follow-up period could be considered short, however, longer follow-up period is often desirable when observing hard outcomes (eg, progression to dialysis, time to first / repeat CV event, death, etc.). This follow-up duration was selected as we recognize that BP is a surrogate outcome and is the most important measure for predicting adverse CKD outcomes. Also, it is well established that reducing high BP among patients with CKD substantially reduces complications and risks of adverse events. Avoiding low BP and resultant adverse effects is also important. However, beyond the scope of this study, we will examine how treatment and monitoring affect hospitalization rates, CV events, and mortality over long term. Second, possible technological pitfalls may provide challenges to conducting this study. We note that frequent monitoring and intervening too aggressively may also cause adverse consequences. Such consequences will be minimized by responding to qualitative feedback, standardizing telemonitoring frequency, ensuring careful monitoring for adverse effects and changing drug regimens as necessary. Third, owning a smartphone and having access to wireless internet is an eligibility requirement for this study and could therefore exclude potentially eligible patients who do not have smartphones. However, as more than 85% of Canadians own a smartphone^
53

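### The defined kidney safety event omits start of kidney replacement therapy, so a patient with a low baseline eGFR who starts dialysis can fall outside the event compared by arm

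*Protocol article*

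**What the plan says.** The kidney event is fixed twice in the protocol article, in matching terms. Study Objectives, secondary aim 5, lists "worsening of kidney function (2x serum creatinine or 50% decline in estimated glomerular filtration rate [eGFR" among the adverse events whose proportion is reported in each arm. Adverse Events and Safety Monitoring lists "worsening kidney function (doubling of serum creatinine or 50% reduction in eGFR from baseline value". Dialysis and transplant appear in neither place.

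Under Study population, the kidney entry criterion is "not on dialysis with eGFR < 60 mL/min/1.73 m"² and/or proteinuria above 1 g/day. The exclusion is "Patients with stage 5 CKD (eGFR ≤ 15 ml/min/1.73 m"², or current kidney replacement therapy. A patient with eGFR just above 15 can therefore be randomized.

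Study Procedures and Data Collection lists creatinine and eGFR at baseline and adds: "These measurements will also be taken at 6-months and 1 year". The statistical section assigns adverse outcomes to Poisson regression with robust error variance, as dichotomous outcomes.

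Kidney failure appears in two other relevant places. Economic Model B considers "the probability of developing end-stage kidney disease (ESKD) (requiring dialysis or transplant") over a lifetime. Potential Challenges and Mitigation Strategies says that a "longer follow-up period is often desirable when observing hard outcomes (eg, progression to dialysis, time to first / repeat CV event, death, etc".

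**The concern.** Both criteria are relative to the patient's own baseline. In a patient who enters with little kidney function, treatment for kidney failure can start before either relative threshold is reached. Once dialysis has started, a later creatinine no longer reflects kidney function alone, so the 6-month or 12-month test need not show a doubling or a halving.

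This event is one of the between-arm measures of harm in a trial whose intervention adjusts blood pressure drugs toward a target. The Discussion names worsening renal function as a consequence of over-treatment that the work should reduce. The definition decides who enters the numerator. A patient who starts dialysis could be classed as having had no worsening of kidney function, in either arm.

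**Working it through.** The article gives no event rate, power or patient count for the kidney event, so there is no figure of its own to reproduce. The sample size of 146 was set on SBP and plays no part here. eGFR is in mL/min/1.73 m² throughout.

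**Inputs from the article.** Eligible baseline eGFR b is above 15. The event is eGFR at or below b/2, or creatinine at least doubled. Tests are at 0, 6 and 12 months.

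**Assumed input.** d is the eGFR at which dialysis starts. The article gives none, so 6, 8 and 10 are shown as a range.

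**Step 1: dialysis before a 50% fall.** The eGFR criterion is missed when d > b/2, that is, when b < 2d.

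| Assumed d | 2d | Eligible baselines that miss the 50% criterion |
|---|---|---|
| 10 | 20 | above 15 and below 20 |
| 8 | 16 | above 15 and below 16 |
| 6 | 12 | none |

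Example: with b = 18 the 50% line is 9. A start at 10 is a fall of 1 − 10/18 = 44%, which is not an event.

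**Step 2: whether the creatinine criterion closes the gap.** Assume eGFR varies as creatinine to the power −k, with k from 1.154 to 1.2. Doubling creatinine is then an eGFR fall of 1 − 2^(−1.154) = 55% to 1 − 2^(−1.2) = 56%. From b = 18 that means an eGFR of 8.1 to 7.8, below the 50% line of 9. On this assumption doubling is the harder criterion to meet, so it rescues none of the cases in Step 1.

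**Step 3: dialysis between tests.** If dialysis starts after one scheduled test and before the next, and the earlier test had not met a criterion, the next creatinine is lowered by dialysis. Neither criterion need then be met. This route does not depend on d, but its frequency cannot be estimated from the article.

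**Step 4: reaching stage 5 without dialysis, for context.** The fall needed to reach 15 is 1 − 15/b: 6.2% from 16, 25.0% from 20, 40.0% from 25, 46.4% from 28 and 50.0% from 30. For any baseline below 30, the article's own stage 5 line is reached before a 50% fall. This gap is wider than the one for dialysis, but it concerns a laboratory category, and from 16 a change of about 6% is enough to cross it.

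**The case against.** The strongest case against is that nothing here is contradictory. The definition can be computed as written, and it sits beside syncope, hypotension and hyperkalaemia as a screen for treatment harm rather than as a progression endpoint. The article itself treats progression to dialysis as a hard outcome better suited to longer follow-up. The adverse event lists are open in wording, the secondary outcome is adverse events reported, and the DSMC reviews data regularly and any case referred to it. Few of 146 patients may have a baseline low enough to matter.

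Much of this stands. A reader might infer that kidney failure would go unseen by the trial or the DSMC. The documents do not support that, because the open lists and DSMC review leave room for dialysis to be reported. A reader might also infer that every crossing of eGFR 15 is a missed serious outcome and belongs in the composite. That does not follow: 15 is an entry exclusion, not a follow-up safety threshold, and Step 4 shows how small a fluctuation could trigger it. Nor is Model B shown to be harmed, since it works with a modelled lifetime probability of ESKD.

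What does not stand is that these points close the gap. The list of events is open, but the kidney definition within it is closed and given numerically in two places, so this is not detail left to a fuller document. The remark on follow-up concerns how long a trial needs to observe hard outcomes; counting a serious event when it occurs is a separate matter. Reliance on unprompted reporting could also differ by arm, because the case manager reviews safety concerns but does not interact with control patients.

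**Conclusion.** The concern holds in limited form. As defined, the kidney event can miss a patient who starts kidney replacement therapy, by either of two routes. The first is confined to low baselines and depends on an assumed eGFR at dialysis start: baselines below 20 for a start at 10, below 16 for a start at 8, none for a start at 6. The second needs dialysis to begin between scheduled tests with no qualifying value beforehand.

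The article does not say how many patients will enter with eGFR between 15 and 20, or below 30, so the number affected is unknown and may be very small. The consequence is confined to a secondary safety comparison. The primary SBP analysis and the sample size do not change.

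**What to change.** For outcome counting only, add start of kidney replacement therapy (dialysis or transplant) as a third component of worsening kidney function, in both Study Objectives and Adverse Events and Safety Monitoring. Leave referral, management and decisions on continued participation as they are.

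Ascertain it from the same source and in the same way in both arms. The Alberta Health linkage planned for costing is one candidate. The renal program database is another, if it records this: the article says only that "Patients with CKD and hypertension will be identified from the Northern Alberta Renal Program (NARP) database", which does not establish that it captures treatment starts during follow-up. Report the three components separately as well as together.

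Do not add a single eGFR of 15 or below to the composite. At most, tabulate follow-up values of 15 or below by arm, as a separate description among patients with baseline below 30.

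The cost is one definition change and one added item of ascertainment, plus confirmation that the chosen source holds the information. Recruitment is unchanged.
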